### Costs

Costs can be grouped into four main categories: initial imaging modalities, medications, hospitalizations and ongoing patient management. The total costs for each patient will be estimated through a simple two-stage process; measurement and valuation of resource use. Following this, the incremental costs associated with the use of CTA will be derived through regression modelling.

#### Measurement of physical quantities of resources consumed

As part of the database constructed for this project, data on the use of health care resources are recorded. Specific resources for which information will be collected are initial imaging modalities, specialist outpatient appointments, family physician consultations, medications, further testing and investigations including invasive coronary angiography and hospitalizations.

#### Valuation of resource use

For all resource items listed above an appropriate unit cost will be derived. Unit costs will be obtained from appropriate provincial fee schedules and administrative data as for project 1A.

#### Costs associated with the use of computed tomographic coronary angiography

The incremental cost associated with the management algorithm that includes the use of CTA will be estimated as follows. A data set will be constructed containing the total costs per patient. For each observation the patient will be assigned a dummy variable relating to whether they were assigned to the management algorithm or to standard care. Regression will be conducted using appropriate generalized linear models controlling for all potential covariates. The appropriate coefficient from the regression will represent the incremental cost associated with the use of CTA.

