**Methods/Design:**

The proposed study aims to provide insight into the efficacy of CTA in HF patients. A multicenter randomized controlled trial will enroll 250 HF patients requiring coronary anatomical definition. Enrolled patients will be randomized to either CTA or ICA (n = 125 per group) as the first test to define coronary anatomy. The primary outcomes will be collected to determine downstream resource utilization. Secondary outcomes will include the composite clinical events and major adverse cardiac events. In addition, the accuracy of CTA for detecting coronary anatomy and obstruction will be assessed in patients who subsequently undergo both CTA and ICA. It is expected that CTA will be a more cost-effective strategy for diagnosis: yielding similar outcomes with fewer procedural risks and improved resource utilization.

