### Primary analysis

Primary analysis will estimate average health care costs per patient for CTA versus ICA. Resource utilization will be measured as detailed below. Cost is defined as the incremental cost of the diagnostic strategy using CTA and will represent the primary outcome measure. Cost will be estimated through regression methods detailed below. Thus, estimations of incremental cost will be evaluated based on costing the components of care.

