### Analysis of uncertainty

Given the complex nature of cost data, generalized linear models (GLMs) will be adopted to determine the incremental costs associated with CTA. GLMs are attractive in the analysis of cost data as these models involve a parametric method where non-normal distributions can be specified and the way the dependent variable and the independent variables interact can be altered [18]. GLMs involve a link function that specifies the relationship between the mean and the covariates and a family, which specifies the assumed mean-variance relationship. Different families and link functions are available. The modified Parks test can be used to determine the appropriate family while the novel technique of extended estimating equations has been developed, which allows identification of both the link function and family [18-20]. The regression model will provide 95% confidence intervals around the estimate of incremental costs. Univariate sensitivity analysis will be conducted to assess the robustness of the study’s results to changing assumptions related to the unit costs of specific resource items. In addition, where available, sensitivity analysis will be conducted utilizing resource use data.

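### The GLM arm coefficient equals the incremental cost only under an identity link, and the plan leaves the link open

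*Protocol article*

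**What the plan says.** All of the text is in the protocol article.

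- **Primary analysis** fixes the target as a cost: "Cost is defined as the incremental cost of the diagnostic strategy using CTA and will represent the primary outcome measure".
- **Costs associated with the use of computed tomographic coronary angiography** gives the model: "Regression will be conducted using appropriate generalized linear models controlling for all potential covariates". Each patient's arm enters as a dummy variable. The section ends with the rule for reading the result: "The appropriate coefficient from the regression will represent the incremental cost associated with the use of CTA".
- **Analysis of uncertainty** describes the link as relating the mean to the covariates and says: "Different families and link functions are available". It offers the modified Parks test for the family and mentions extended estimating equations, "which allows identification of both the link function and family".
- The same section gives the interval: "The regression model will provide 95% confidence intervals around the estimate of incremental costs".

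No section fixes an identity link. None mentions back-transformation, marginal effects or averaging of predicted costs.

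**The concern.** The reading rule and the open link do not fit together. The rule equates one coefficient with a difference in mean cost, which is true for one link only. The next section presents freedom over the link as a merit of the method.

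The trial's primary estimate is at stake. An analyst who follows the text under a log link would report a log ratio of mean costs as a cost per patient. One who sees the problem would have to choose a conversion after the data are in. That choice matters because, under a non-identity link with covariates, the money difference depends on the patients over whom it is averaged. The Sample size section expects room for at least 25 coefficients, so there is real covariate variation to average over.

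**Working it through.** **1. The plan's own figure.** Inputs from Sample size and Design: 125 patients per arm, coefficient of variation (CV) 25%, cost reduction 10%. Alpha and sidedness are not stated, so I assume a two-sided 0.05.

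- Standard error relative to the mean: 0.25 × √(2/125) = 0.0316.
- Power: Φ(0.10/0.0316 − 1.96) = Φ(1.20) = 88.5%. One-sided at 0.05 it is 93.5%.

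This agrees with the article's claim of sufficient power. The present point does not touch it.

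**2. What the coefficient is.** For link g, the model is g(mean cost) = a + b·arm + covariate terms. At equal covariates, b = g(μ_CTA) − g(μ_ICA). This equals μ_CTA − μ_ICA for the identity link and not for the other links in step 3.

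**3. Size by link.** The article gives no mean cost, so I assume ICA means of 5,000, 10,000 and 20,000, with a true 10% reduction.

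| Link | Coefficient | 5,000 | 10,000 | 20,000 |
|---|---|---|---|---|
| Identity | 0.9m − m | −500 | −1,000 | −2,000 |
| Log | ln 0.9 | −0.105 | −0.105 | −0.105 |
| Square root | √(0.9m) − √m | −3.63 | −5.13 | −7.26 |
| Inverse | 1/(0.9m) − 1/m | +0.0000222 | +0.0000111 | +0.0000056 |

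Only the first row is a cost. In the last row the sign reverses. For true reductions of 20% and 30% the log-link coefficients are ln 0.8 = −0.223 and ln 0.7 = −0.357.

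**4. The interval that goes with the coefficient.** Under a log link at CV 25%, the standard error is about 0.0316. The 95% interval is −0.105 ± 1.96 × 0.0316, or −0.167 to −0.043. Exponentiated, this is a cost ratio of 0.90 (0.846 to 0.958). It becomes money only when combined with a mean cost.

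**5. Dependence on case mix.** Under a log link, a patient with predicted ICA cost m has a difference of m × (0.9 − 1) = −0.1m. If half the patients had m = 5,000 and half 20,000, the average would be (−500 − 2,000)/2 = −1,250. The coefficient would still be −0.105.

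**6. Does averaging predicted costs recover the target?** I used 1,000 simulated trials of 250 patients with gamma costs, a log link, one covariate, an assumed ICA mean of 10,000 and a true difference of −1,000. Each patient's cost was predicted under both arms, averaged and subtracted, with a delta-method interval.

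| CV | Mean estimate | Mean SE | 95% interval covers −1,000 |
|---|---|---|---|
| 25% | −1,008 | 300 | 95.0% |
| 100% | −1,001 | 1,198 | 94.8% |

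The raw coefficient's interval never contained −1,000. That only restates the mismatch of units; it does not show that the model fits badly.

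**The case against.** The strongest reply is that the text is loose rather than wrong. The target is named as incremental cost in more than one section, the interval is said to lie around incremental costs and not around the coefficient, and the authors plainly know what a link function does. An identity link with a non-normal family would satisfy every sentence. A condensed article may also leave the conversion method to an analysis plan that is not shown.

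Part of this stands. Four stronger readings are tempting, and the documents do not support them:

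- **That the plan commits to choosing the link from the data.** The wording is permissive. The modified Parks test is offered as an option, and for the family only. Extended estimating equations are described as available, not adopted.
- **That the reported interval will certainly be on the wrong scale.** It follows only if the model's own interval for the coefficient is used under a non-identity link.
- **That the interval is materially too narrow because it ignores model selection.** Nothing here shows a size for that effect. The simulation fitted one fixed link and family and did not study selection.
- **That the primary comparison or the power fails.** For a fixed link, a zero coefficient still means equal mean costs at equal covariates, so the test of no effect stays valid.

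The reply does not rescue the sentence itself. It states what the coefficient represents, so it is not a detail left for later. The word *appropriate* does not help either: under a log, square-root or inverse link, no single coefficient is the cost difference.

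**Conclusion.** The point holds in conditional form. The rule for reading the primary estimate is right under an identity link and wrong under the other links examined, and the plan does not fix the link. If a log link were used and the text followed, a true 10% saving would be reported as −0.105 instead of a money amount, which would be −1,000 at an assumed ICA mean of 10,000. The money figures rest on assumed means, and the simulation on gamma costs with one covariate. The algebra rests on neither. Because the sentence governs the primary outcome, it should be corrected before analysis.

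**What to change.** Replace the last sentence of the section on costs associated with the use of CTA by one of two rules:

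1. Pre-specify an identity link, so that the arm coefficient is the incremental cost; or
2. Define the incremental cost as the difference in mean predicted cost if all intention-to-treat patients were assigned to CTA and if all were assigned to ICA (recycled predictions). Give a delta-method or bootstrap 95% interval on that cost scale.

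Align the interval sentence in Analysis of uncertainty with the rule chosen.

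Three refinements are optional. If link or family is in fact selected from the data, the selection can be repeated in each bootstrap resample, at the price of a possibly slightly wider interval. Selection can be made blind to arm. An unadjusted mean difference can be reported alongside.

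The cost is a few sentences and a few lines of code. No patients or data are added, and randomization and sample size do not change.

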### Analysis of uncertainty

Given the complex nature of cost data, generalized linear models (GLMs) will be adopted to determine the incremental costs associated with CTA. GLMs are attractive in the analysis of cost data as these models involve a parametric method where non-normal distributions can be specified and the way the dependent variable and the independent variables interact can be altered [18]. GLMs involve a link function that specifies the relationship between the mean and the covariates and a family, which specifies the assumed mean-variance relationship. Different families and link functions are available. The modified Parks test can be used to determine the appropriate family while the novel technique of extended estimating equations has been developed, which allows identification of both the link function and family [18-20]. The regression model will provide 95% confidence intervals around the estimate of incremental costs. Univariate sensitivity analysis will be conducted to assess the robustness of the study’s results to changing assumptions related to the unit costs of specific resource items. In addition, where available, sensitivity analysis will be conducted utilizing resource use data.

### Missing data

‘Missingness’ is considered to be missing at random (MAR) and mixed methods repeated measures (MMRM) and multiple imputation (MI) techniques will be used for handling missing data. In particular, for continuous outcomes at multiple time points, MMRM will be used.

### Study management

The IMAGE-HF trial is managed by an Executive Committee consisting of clinicians specialized in diagnostic imaging and heart failure and experts in biostatistics, physics and radiochemistry, as well as a larger Steering Committee consisting of members of the Executive Committee and representatives of all the initial study centers. In addition, an events adjudication committee (blinded to patient allocation) will independently review and adjudicate each clinical event. Since all the imaging approaches are part of standard clinical practice, no interim analysis is planned, but there will be independent data safety monitoring board (DSMB), which will review the safety data on a periodic basis.

## Discussion

The proposed RCT is the largest RCT in HF patients to compare CTA versus ICA. This RCT will accomplish several goals: 1) it will determine feasibility and diagnostic accuracy of CTA in patients with undifferentiated heart failure; 2) if feasible, it will determine if the incorporation of CTA into the investigation algorithm of HF patients is cost-effective; and 3) it will determine if the CTA strategy, compared to ICA, is safe.

If these hypotheses are supported, study findings will have significant implications related to clinical practice. Evidence that CTA is effective in distinguishing etiology of HF at a lower cost with reductions in unnecessary ICA testing, subsequently with fewer procedure-associated complications, would be very attractive to clinicians and patients. This may further contribute to a reduction in healthcare costs and reduce current burdens on healthcare systems worldwide.

## Trial status

This randomized clinical trial is currently recruiting subjects.

## Abbreviations

CAD: Coronary artery disease; CCE: Composite clinical events; CTA: Tomographic coronary angiography; DSMB: Data safety monitoring board; GFR: Glomerular filtration rate GLMs, generalized linear models; HF: Heart failure; HR: heart rate; ICA: Invasive coronary angiography; ITT: Intention-to-treat; MACE: Major adverse cardiac events; MRI: Magnetic resonance imaging; QoL: Quality of life; RCT: Randomized controlled trial; RNA: Radionuclide angiography; ROC: Receiver operating characteristic; VD: Vessel disease.
